#### **Polysomnography (PSG)**

Polysomnography is an overnight recording of sleep pattern and behaviors associated with sleep. A variety of sensors are applied with paste or tape to the body's surface to record brain waves, eye movements, muscle tone, body movements, heart rate, and breathing. The recording of the sensors can be helpful in determining sleep latency (the time that transpires between lights off and the onset of sleep), total sleep time, the time spent in each sleep stage, number of awakenings, WASO, and sleep efficiency (the ratio of total sleep time to time spent in bed, multiplied by 100). Normal sleep is separated into non-rapid eye movement (NREM) and rapid eye movement (REM) sleep. NREM sleep is further divided into 4 stages advancing from alert to asleep, with the lightest sleep occurring in Stage I sleep, and the deepest sleep occurring in Stage IV NREM sleep. NREM and REM sleep follow continuous cycles at approximately 90-minute intervals throughout the night. In addition, a diagnostic PSG includes channels to monitor air flow and limb movement to generate an AHI score and PLMAI score for evidence of sleep apnea and restless leg syndrome, respectively. A diagnostic PSG will be done on all patients on the first night of the placebo lead-in period. The diagnostic PSG will initially be scored locally by the site to determine if the patient still qualifies. The dPSG will be re-scored by the central facility. The rest of the PSGs will be done according to the schedule of evaluations (see [Table 2](#)) and scored by a central facility.

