#### **14.1.1. General**

The primary efficacy variable is the average Latency to Persistent Sleep (LPS) computed via PSG assessments from nights 1 and 8. The primary null hypothesis to be tested is that there are no differences among the treatments.

Statistical analyses will be performed using two-sided test. A 0.05 significance level will be used in all tests of treatment differences. Test for interaction will utilize a 0.10 statistical significance level.

For the primary efficacy endpoint, the type I error will be controlled via Fisher's protected least significant difference (LSD). Using this procedure, an overall test of the treatment effect will be conducted and pairwise comparisons will be examined only if the overall treatment is significant at the 0.05 alpha level. Pairwise comparisons will also be examined at the 0.05 significance level.

In addition, for labeling purposes only, the experiment wise Type I error will be controlled to a maximum of 5%. A gatekeeper strategy will be employed such that any secondary endpoints will be considered for statistical significance only if the primary endpoint to be statistically significant.

Data will be summarized by treatment group (and by visit when applicable), with respect to demographic and baseline characteristics, efficacy variables, and safety variables.

Summary statistics will include the mean, N, standard deviation, median, minimum, and maximum values for continuous variables, and frequencies and percentages for categorical variables.

Continuous variables such as latency to persistent sleep (LPS), wake after sleep onset (WASO), total sleep time (TST) and sleep efficiency (SE) will be analyzed using an ANCOVA model with treatment and pooled center as main effects, baseline as a covariate and the treatment-by-baseline interaction. An exploratory analysis will be performed to explore whether there are treatment-by-center interactions. If a treatment-by-center interaction is detected, the interaction will be explored in an ad-hoc manner.

Categorical variables will be analyzed using Cochran-Mantel-Haenszel (CMH) test blocking on centers (or pooled centers).

Details of the model and the analyses will be specified in the SAP. All statistical analyses will be performed using SAS®, Version 8.2 or higher.

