#### **14.9.1.2. Secondary Efficacy Outcomes**

The secondary efficacy variables are:

- the average WASO, TST and SE as measured by PSG on Nights 1 and 8.
- the average LPS, WASO, TST and SE as measured by PSG on Nights 22 and 29
- the LPS, WASO, TST and SE as measured by PSG on Nights 1, 8, 22 and 29
- rebound effects through the LPS, WASO, TST and SE as measured by PSG on Night 36
- subjective assessments such as: sleep quality, depth of sleep, sleep latency (sSL), total sleep time (sTST), daytime function and daytime alertness
- residual effects through DSST score and VAS score
- subjective withdrawal symptoms after 5 weeks of VEC-162 treatment as measured by the benzodiazepine withdrawal symptom questionnaire (BWSQ)
- contribution of a PER3 gene polymorphism on the primary and secondary efficacy endpoints.

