###### **14.9.2.2. Statement of the Null and Alternate Hypotheses**

Statistical analyses will be performed using two-sided test. A 0.05 significance level will be used in all tests of treatment differences. Test for interaction will utilize a 0.10 statistical significance level.

The type I error will be controlled via Fisher's protected least significant difference (LSD). Using this procedure, an overall test of the overall treatment effect will be conducted and pairwise comparisons will be examined only if the overall treatment is significant at the 0.05 alpha level. Pairwise comparisons will also be examined at the 0.05 significance level.

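### The gate on the primary endpoint does not deliver the stated 5% experiment-wise Type I error for labeling once LPS is truly improved

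*Protocol*

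**What the plan says.** Protocol 14.1.1 (General) makes a quantitative commitment: "for labeling purposes only, the experiment wise Type I error will be controlled to a maximum of 5" percent. It then names the mechanism, a gatekeeper strategy under which "any secondary endpoints will be considered for statistical significance only if the primary endpoint to be statistically significant".

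The rules around that commitment are:

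- **Level per test.** 14.1.1 and 14.9.2.2 both set it: "A 0.05 significance level will be used in all tests of treatment differences".
- **Doses within an endpoint.** 14.1.1 says "For the primary efficacy endpoint, the type I error will be controlled via Fisher's protected least significant difference (LSD"). 14.9.2.2 repeats the method without limiting it to the primary: "The type I error will be controlled via Fisher's protected least significant difference (LSD").
- **Secondaries.** 14.9.1.2 lists "the average WASO, TST and SE as measured by PSG on Nights 1 and 8", the Night 22/29 averages of LPS, WASO, TST and SE, then "the LPS, WASO, TST and SE as measured by PSG on Nights 1, 8, 22 and 29", followed by Night 36, subjective, residual-effect, withdrawal and PER3 items. 14.9.2.4 gives continuous secondaries a model like the primary's. Neither section gives an order, an alpha split or an adjustment.
- **SE.** Section 11.1 defines "sleep efficiency (the ratio of total sleep time to time spent in bed, multiplied by 100"). The recording lasts 8 hours.

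**The concern.** A maximum on experiment-wise error is a claim about every combination of true and false null hypotheses. A single gate secures it for one kind of combination only, the one in which the primary null is true, because a false secondary claim then first needs a false primary result. If the drug works on LPS, the gate is open almost always and each secondary is then tested at 0.05 in its own right. LSD limits the error between doses within one endpoint and does nothing between endpoints.

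An effective primary is also the situation in which labeling claims on secondaries would be made, and the one the trial is powered for. WASO, TST and maintenance-of-effect results could then be presented under a 5% guarantee that the stated procedure does not provide.

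**Working it through.** **Inputs.** Three arms, 1:1:1, 108 per arm; planned LPS difference 15 minutes with SD 30, so 15/30 = 0.5 SD (14.2). Two-sided 0.05 per test (14.1.1). LSD inside each endpoint, which is the reading of 14.9.2.2 more favorable to the plan. Endpoints are taken as normal and equally correlated. The protocol gives no correlations, so 0, 0.5 and 0.7 are assumptions.

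**Endpoints counted.** The averaged PSG secondaries are WASO, TST and SE on Nights 1/8 (3) and LPS, WASO, TST and SE on Nights 22/29 (4). With 8 hours (480 minutes) in bed, SE = 100 × TST/480, so SE and TST carry the same test. Leaving SE out gives 2 + 3 = 5 distinct endpoints.

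**Step 1: where the 5% holds.**

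- Primary alone: simulated LSD with three arms gives 5.0% in every configuration tried (all arms equal, or one arm different with the other two equal).
- All nulls true: the primary shows a false dose-versus-placebo difference about 4% of the time, so a false secondary claim cannot be more frequent than that. With as many as 36 secondaries the simulated rate is about 3.5%. Weak control holds.

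**Step 2: LPS effective, secondaries null.** With a 0.5 SD effect in both doses, the gate opens in about 97% of simulated trials. For one null endpoint, LSD gives a false dose-versus-placebo claim with probability of about p = 0.042. This is the 4% of Step 1; it is below 5% because some significant overall tests lead only to a difference between the two doses. For K independent endpoints with the gate open:

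P(at least one) = 1 − (1 − p)^K

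- K = 2: 1 − 0.958² = 0.082
- K = 5: 1 − 0.958⁵ = 0.193

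Simulation supplies the correlated cases:

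| Null secondaries, LSD in each, gate open | r = 0 | r = 0.5 | r = 0.7 |
|---|---|---|---|
| 5 distinct averaged PSG endpoints | 19% | 16% | 13% |
| WASO and TST, Nights 1/8 only | 8% | 8% | 7% |

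These figures take the gate as certain to open. In a 200,000-trial check that also required the primary to succeed at the planned effect, the first row became 19%, 15% and 12%, and the second 8%, 7% and 6%. All remain above 5%.

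**Step 3: does a fixed sequence restore the property?** I tested LPS, WASO and TST on Nights 1/8, then LPS, WASO and TST on Nights 22/29, each by LSD at 0.05, going on only if both doses beat placebo. The simulated chance of any false dose-versus-placebo claim was 3% to 5% in every configuration tried, including those with one effective dose.

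**The case against.** The strongest reply is that the protocol leaves detail to the SAP. Section 14.1 describes the analyses in general terms, and the gate is worded as a necessary condition, not a sufficient one. A fixed sequence at 0.05 per step could be added in the SAP without contradicting any sentence here. That is true, and the absence of a testing order alone would not be a finding. But the protocol goes further: it states the numerical maximum, names the mechanism and fixes the level of every test, and that procedure as written does not have the stated property. Later detail may repair it; the statement still needs correcting.

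Several stronger readings are tempting and are not supported:

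- *Error of 77% over 36 endpoints, or 48% over 7 without LSD.* The 36 (3+4+16+4+6+2+1) include rebound, residual-effect and withdrawal measures, which the Synopsis lists under Safety, although 14.9.1.2 lists them as efficacy outcomes. They also count SE apart from TST, and single nights alongside the averages built from them. Both figures assume independence, and the 48% ignores the unrestricted LSD statement in 14.9.2.2.
- *No valid error control at all.* Weak control exists, and LSD with three arms is valid for the primary.
- *A dose that fails on LPS may claim secondaries.* The gate refers to the primary endpoint without mentioning doses. That is an ambiguity, not a permission.
- *Reporting both SE and TST inflates the error.* Two perfectly correlated tests add nothing to it. The matter is one of redundant claims.

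**Conclusion.** The concern holds in this limited form. The 5% maximum in 14.1.1 is true when the primary null is true and false when LPS is improved and the labeling secondaries are null. For the five distinct averaged PSG secondaries the error is about 19%, 16% or 13% at correlations of 0, 0.5 or 0.7; for WASO and TST on Nights 1/8 it is about 7-8%.

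The size depends on the assumed correlations, on LSD being applied to every endpoint and on which secondaries are meant for labeling, which the protocol does not say. Few and very highly correlated endpoints shrink the excess: two endpoints at correlation 0.9 give about 6% with the gate open. The direction does not depend on counting safety-type measures or on assuming independence. A reader might infer that the primary conclusion or the sample size is in doubt. Neither is: 86 per arm gives 90.3% power by the t-test, 86/0.8 = 107.5 rounds up to 108, and 3 × 108 = 324.

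**What to change.** Choose one of two corrections, before the blind is broken:

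1. **Restate the claim.** Delete the experiment-wise sentence, or limit it to the primary endpoint, noting that the gate gives only weak control beyond it. Report all secondaries as nominal.
2. **Make the claim true.** Name a short ordered list of labeling secondaries tested in fixed sequence after LPS on Nights 1/8, each by LSD at 0.05. The order already in 14.9.1.2 would serve: WASO and TST on Nights 1/8, then LPS, WASO and TST on Nights 22/29, with SE left out as a rescaling of TST. State what happens when only one dose succeeds: for example, both doses must succeed to go on, or a Bonferroni-based graphical procedure by dose lets one proceed alone. All other secondaries are nominal.

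The sequence in option 2 is one of several valid procedures. Either option changes only protocol or SAP wording and leaves the primary analysis and sample size as they are. The price is that fewer secondaries can be called confirmatory, and in a fixed sequence a failure at one step closes every later one.

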## 14.2. Sample Size and Accrual

The sample size is based on the average LPS computed via PSG assessments from nights 1 and 8. Based on a t-test to detect a 15 minute difference between VEC-162 treated patients and placebo patients, and assuming a common standard deviation of 30 minutes, a sample size of 86 patients per treatment arm is needed in order to have 90% power with a two-sided alpha of 0.05. The standard deviation is based on data found in literature. Considering a 1:1:1 randomization between VEC-162 20mg, VEC-162 50mg and placebo, and a 20% drop-out rate, a total of 324 patients (108 per arm) will be needed.

A re-estimation of the sample size will be done through an adjusted one-sample variance procedure. In this procedure, a blinded variance estimation is obtained by adjusting the one-sample variance of the pooled sample.

Let  $N$  and  $VAR$  be the respective preliminary sample size and variance originally estimated (as per above). Let  $N(s)$  and  $VAR(s)$  be the respective sample size and variance of the pooled blinded sample at this sample-size re-assessment look. Then according to Zucker et al. (13), the following estimation of the variance ( $VAR(adj)$ ) will be used to generate an adjusted sample size  $N(adj)$ ;

$$VAR(adj) = VAR(s) - N(s) D^2 / 2(2N(s)-1),$$

where  $D$  is equal to a 15 point change from baseline

$N(adj)$  will then be generated using a two-group t-test procedure with a 0.05 two-sided significance level and the variance  $VAR(adj)$ .

Since this sample size re-assessment is not intended to stop the trial early due to efficacy but only to provide a variance re-estimation and a sample size recalculation, then after the recruitment of the first  $n(s)$  patients,

- if  $N(adj) \leq N$ , then a further  $N-N(s)$  patients will have to be recruited until the initially planned sample size  $N$  is reached.
- Otherwise if  $N(adj) > N$ , then a further  $N(adj)-N(s)$  patients will have to be recruited.

As the procedure does not require unblinding of the treatment code during the ongoing trial nor produce any estimation of a treatment effect hypothesis testing, then no adjustment to control the nominal significance level is required.

The required sample size could also be adjusted if the drop-out rate differs from the estimated drop-out rate. This change would be made via a protocol amendment.

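### Section 14.2's sample-size re-estimation rule puts N, N(s) and N(adj) on inconsistent scales, and no literal reading makes both its comparison and its recruitment step work

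*Protocol*

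**What the plan says.** All of this stands in Protocol section 14.2.

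- **Initial size.** The calculation is "Based on a t-test to detect a 15 minute difference between VEC-162 treated patients and placebo patients", "assuming a common standard deviation of 30 minutes", and 86 per arm "is needed in order to have 90% power with a two-sided alpha of 0.05". With 1:1:1 allocation and 20% drop-out, "a total of 324 patients (108 per arm) will be needed".
- **Symbols.** N and VAR are the preliminary size and variance from the text above; no figure is attached to N. N(s) and VAR(s) are said to "be the respective sample size and variance of the pooled blinded sample at this sample-size re-assessment look".
- **Variance correction.** VAR(adj) = VAR(s) − N(s)D²/[2(2N(s)−1)], where D "is equal to a 15 point change from baseline".
- **New size.** N(adj) "will then be generated using a two-group t-test procedure with a 0.05 two-sided significance level and the variance" VAR(adj).
- **Decision.** If N(adj) ≤ N, a further N − N(s) patients are recruited, up to the planned N. If N(adj) > N, a further N(adj) − N(s) are recruited.

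**The concern.** The recruitment step only makes sense with whole-trial counts. N(s) is the pooled sample, and it is subtracted from N to give the number of patients still to recruit. The only whole-trial figure printed in the section is 324, which already contains three arms and the drop-out allowance. N(adj) has neither: it is described only as the output of a two-group t-test, and no power is named for it. The variance correction adds a third inconsistency, because its algebra is that of a two-arm trial with N(s) counted per arm.

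The look exists to protect the 90% power against a wrong SD, and the assumed SD comes only from literature. If the two sides of the comparison are on different scales, the look can report that no increase is needed when the plan's own recipe says one is.

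**Working it through.** **Inputs (section 14.2):** difference 15 minutes, SD 30 minutes, two-sided alpha 0.05, power 90%, three arms, 20% drop-out. The re-estimation text names no power; I assume 90% carries over.

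**Formula.** With n per arm, df = 2n − 2 and noncentrality = 15/[SD × √(2/n)], power comes from the noncentral t distribution, and the required n is the smallest that reaches 90%.

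**The plan's figure reproduces.** At SD 30, n = 85 gives 89.99% and n = 86 gives 90.3%. Then 86/0.8 = 107.5, rounded up to 108, and 3 × 108 = 324.

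**Best-fitting reading: two-group total 2n against N = 324.** The matched need is 3 × ceil(n/0.8).

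| SD | n per arm | 2n | Increase? | Matched need | Power with 324 kept (86 / 108 evaluable per arm) |
|---|---|---|---|---|---|
| 30 | 86 | 172 | no | 324 | 90% / 95% |
| 35 | 116 | 232 | no | 435 | 80% / 88% |
| 40 | 151 | 302 | no | 567 | 69% / 78% |
| 41.5 | 162 | 324 | no | 609 | 65% / 75% |
| 42 | 166 | 332 | yes, by 8 | 624 | 64% / 74% |

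The last column is the power before any increase; at SD 42 the 8 extra patients hardly change it. At the planned SD the rule sets 172 against 324, so it does not return its own starting value. When it does trigger, it undershoots.

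**Other readings.** Each row gives the largest SD, searched in steps of 0.05 minutes, at which the rule calls for no increase.

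| N(adj) against N | No increase up to SD | Power there (86 / 108 per arm) |
|---|---|---|
| n against 86 | about 30.15 | 90% / 95% |
| 3 × ceil(n/0.8) against 324 | about 30.15 | 90% / 95% |
| 3n against 324 | about 33.85 | 82% / 90% |
| 2n against 258 (= 3 × 86) | about 37 | 75% / 84% |
| n against 324 | about 59 | 38% / 46% |

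The first two rows trigger where they should. The second needs a three-arm and drop-out step that the text does not contain. The first fails at the recruitment step. With N = 86 and N(s) pooled, N − N(s) is negative once more than 86 patients are in the sample. If N(s) is instead taken per arm, against its definition, recruitment ends at 86 per arm, or 258, which contradicts 324. After 20% drop-out that leaves 0.8 × 86 = 68.8, about 69 per arm, and 83% power even at SD 30.

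**Variance correction.** In two arms of m patients each, with means D apart, the between-arm sum of squares is mD²/2. Dividing by 2m − 1 gives the printed term, so the formula is right for N(s) = m per arm. For a pooled three-arm sample the term tends to:

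- means (0, D, D): 2D²/9 = 2 × 225/9 = 50;
- means (0, D/2, D): D²/6 = 225/6 = 37.5.

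The printed formula tends to D²/4 = 56.25. Against a variance of 900 the excess is 6.25/900 = 0.7% to 18.75/900 = 2.1%, which is small.

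**The case against.** The strongest reply is that the section never says N is 324, nor that N(adj) is a two-group total. The number first derived from the variance is 86 per arm, itself from a t-test. Repeating that test with VAR(adj) gives another per-arm number, and comparing it with 86 is like for like. The variance formula also uses a per-arm count. This stands as far as the trigger goes, so a reader who infers that the protocol definitely compares a two-group number with 324 goes further than the text. It does not rescue the rule, because the recruitment step then breaks down as shown above.

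A reader might also infer that the trial would be badly underpowered. The documents do not support that as a general statement:

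- No passage suggests an SD near 40.
- The Full Analysis set (section 14.4) needs one dose and post-baseline PSG. Night 1 PSG follows the first dose, and a missing Night 8 is filled from Night 1 (section 14.9.2.1). Few patients may be lost to the primary analysis, so the power figures for 108 per arm are probably closer.
- The primary model is an ANCOVA with baseline. If 40 is the raw SD and the baseline correlation is 0.3 to 0.5 (my assumption; the protocol gives none), the residual SD is 40 × √(1 − r²) = 38.2 to 34.6, and 108 per arm gives about 82% to 89%.

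Finally, no printed sample-size figure is wrong, and the rule can never take the trial below its planned size. Both points are correct. The defect lies in the rule, not in the 324.

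**Conclusion.** The rule is wrong as written. Its three size symbols are on mixed scales, N(adj) has no stated target power, and no literal reading makes the comparison and the recruitment step work together. This cannot wait for the SAP: the rule is printed in the protocol and acts on recruitment during the trial, whereas section 14.1 requires the SAP only before database lock.

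The size of the harm is conditional. On the reading that fits the recruitment wording best, no increase occurs until the SD is about 41.5, against just above 30 on matched scales; other readings move that point anywhere from about 34 to 59. Nothing is lost if the SD is 30 or less. The power ranges assume a 15-minute effect, 90% power as the target for N(adj), and between 86 and 108 evaluable patients per arm. The variance correction and the description of D are minor: D has the right value, 15, but is called a change from baseline where the formula needs a between-arm difference.

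**What to change.** Amend section 14.2 as follows.

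1. State that n(adj) per arm comes from the two-group t-test at 90% power, two-sided 0.05, a 15-minute difference and VAR(adj).
2. Set N(adj) = 3 × ceil(n(adj)/0.8) and compare it with N = 324.
3. Define N(s) as the pooled count over the three arms, so that N − N(s) and N(adj) − N(s) are patients still to recruit.
4. Define D as the 15-minute difference between active drug and placebo.
5. Either use VAR(s) unadjusted, which is slightly conservative, or use a three-arm correction and state the assumed effect pattern. If both doses have the full effect, it is VAR(s) − 2N(s)D²/[9(N(s)−1)]; this over-subtracts if one dose does less.

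The cost is a few lines of text. The initial 324 does not change, and the look stays blinded. The real cost arises only if the SD is above plan: the increase can be large (435 at SD 35, 567 at SD 40), but holding 90% power at the larger SD is what the look is for.
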